### Statistical Analysis

We calculated our required sample size using G^*^Power 3.1 (51) (ANOVA: Repeated measures, three groups, four measurement points; effect size F = 0.25; < = 0.05; Power = 0.80; number of groups = 3). Based on that calculation, at least 90 participants (30 in each study arm) completing the intervention are required in order to detect small to moderate size differences. Cohen's d (effect size) will be used to compare the percentage of variation in the groups before and after treatment.

All data sets of participants will be analyzed, on an intention to treat basis. Data at baseline, second week and after the intervention, as well as at 6 and 12-months post-intervention will be considered (see Table 3). The demographic and clinical characteristics of the sample will be compared at baseline using an analysis of variance (ANOVA), except for gender and age, which will be assessed using an analysis of covariance (ANCOVA). To compare the overall effect of treatment over time in the three groups, data from the full intent to treat sample will be analyzed using a repeated-measures analysis of variance (ANOVA) with treatment as the intergroup factor and time as the intrasubject factor. *Post-hoc* analyses will be performed using Student's *t*-test for intergroup comparisons. Reported adverse effects and safety-related events will be analyzed separately as will withdrawal from the study or treatment group changes.

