### Participants Switching Groups, Drop-Outs, and Missing Data

Drop-outs will be replaced until the calculated number of participants has completed the intervention; all enrolled participants will be allowed to complete the intervention. Patient switching therapeutic arm will be considered as drop-outs and will be replaced correspondingly; however, they will be allowed to complete the intervention and outcomes will be assessed as scheduled. For all dropouts, an additional intention to treat, and last observation carried forward analysis will be performed.

In contrast to drop-outs the assessment of outcomes and observation of participants switching groups will be continued. Data prior to switching will be analyzed and reported separately in order to avoid bias duplication of results for a particular participant.

The outcomes of those participants who completed the intervention after switching groups will undergo a *post-hoc* analysis with those who completed their treatment intervention without switching. A multivariate analysis of variance (MANOVA) will be performed, taking into account the switch of intervention together with outcomes measured pre- and post-intervention; i.e., ignoring the outcomes at week two for those not switching intervention arm. Groups for analysis will be constructed according to the number of participants actually switching interventions: the effect of the four first sessions will be categorized according to the change and included in the analysis.

If a participant withdraws from the study, his data will be anonymized, and his name will be deleted permanently from the study.

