The assessment of outcomes uses a variety of instruments measuring symptom load, neuro-cognitive performance and psychosocial functionality since we expect each treatment arm to show a unique response profile (11). For symptom load, we have chosen to use the PANSS, since it is considered the most specific and validated scale for measuring change in patients with a schizophrenic psychosis (62, 63). The MCCB is regarded as the standard test battery for use with patients diagnosed with schizophrenia; it is claimed as both robust to learning effects and sensitive to change (47). Taking into account that improvements in symptomatology and neuro-cognition should lead to increased autonomy, we have chosen the mini-ICF-APP to assess psychosocial-functioning independently of the main diagnosis (40, 64, 65). Using this set of outcome measures, we expect to assess all facets of the interventions, whilst facilitating the interpretation and comparison of our results with those from previous studies (63).

We anticipate an overall improvement in all participants, regardless of group allocation. This may be attributable to pharmacological treatments administered to the participants. For the same reason, we do not anticipate significant differences in symptom load. However, we do not exclude to find differences in dose equivalents of administered medication, primarily antipsychotics and benzodiazepines. Furthermore, we hope for a reduction of polypharmacy. In order to quantify this effect; medication, respectively dose and dose equivalents, will be taken into account as possible confounders (66). Pharmacological treatment will not be restricted since we consider withholding or delaying pharmacological treatment for methodological or design purposes to be unacceptable; furthermore, in clinical practice, psychological interventions are used as an add-on to pharmacological therapy (11). Offering just a single psychotherapeutic treatment could be ineffective for some patients and at worst detrimental, which could lead to treatment abandonment (67). An intervention which is neither accepted nor tolerated by participants should not be imposed on them.

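### Drop-outs appear not to be followed up, and the planned repeated-measures ANOVA with an additional LOCF analysis cannot deliver the promised intention-to-treat comparison

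*Protocol article*

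**What the plan says.** Under Statistical Analysis, the main comparison of the three arms is described thus: "data from the full intent to treat sample will be analyzed using a repeated-measures analysis of variance (ANOVA"), with treatment as the between-subject factor and time as the within-subject factor. The visits are baseline, week 2, post-treatment, 6 months and 12 months.

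Under Participants Switching Groups, Drop-Outs, and Missing Data, the article treats two kinds of participant differently: "In contrast to drop-outs the assessment of outcomes and observation of participants switching groups will be continued". The same section counts switchers as drop-outs for replacement, but says that they will be assessed on schedule. The Discussion repeats that they count as drop-outs in the primary analysis. On missing values the section says only: "For all dropouts, an additional intention to treat, and last observation carried forward analysis will be performed". It ends with a rule for participants who withdraw from the study, but does not say whether stopping therapy is the same as withdrawing.

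The Discussion expects everyone to get better: "We anticipate an overall improvement in all participants, regardless of group allocation". It also says that negative and cognitive symptoms can make therapy hard to cope with and so lead to drop-out.

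**The concern.** If assessment stops when therapy stops, the post-treatment, 6-month and 12-month outcomes of those participants are never collected, and no later analysis plan can recover them. The full intention-to-treat sample can then enter a classical repeated-measures ANOVA only with imputed values. Without imputation, the analysis covers participants seen at all five visits, a group selected after randomisation by a process that the article itself links to symptoms. With LOCF, a participant who leaves early keeps an early, largely unimproved score up to 12 months. In a population that improves, this makes the arm that loses more people, or loses them earlier, look worse whatever its efficacy. The arm comparison could then reflect retention rather than treatment.

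**Working it through.** **The plan's own figure.** The only calculation in the article is the sample size: "ANOVA: Repeated measures, three groups, four measurement points", "effect size F = 0.25; < = 0.05; Power = 0.80; number of groups = 3", leading to "at least 90 participants (30 in each study arm) completing the intervention are required". Reading the garbled symbol as alpha = 0.05 and testing the between-arm effect, λ = N f² m / (1 + (m − 1)ρ), with 2 and N − 3 degrees of freedom. At ρ = 0.40, λ = 90 × 0.0625 × 4 / 2.2 = 10.2 and power is 0.81, so 90 is reproduced for ρ of about 0.40 to 0.41. At ρ = 0.5 the same formula needs 102, and at ρ = 0.3 it needs 78. The article does not state ρ or the effect tested. It gives no drop-out rate, so this figure neither supports nor weakens the present point.

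**Completer analysis.** Recruitment continues until 30 per arm complete. If 30% of an arm dropped out (assumed), 30 / 0.70 ≈ 43 would be randomised and about 13 of the 43 would have no complete row.

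**What the article expects on retention.**
- Expected Outcomes, text: similar in all arms; then slightly higher for IPT, followed by INT and CGP.
- Table 5, combined drop-out and switching row: INT +++, IPT ++, Cogpack +.
- Table 5, completion of therapy: INT ++, IPT ++, Cogpack +++.

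The text puts CGP last for retention, while Table 5 puts it first for completion. These cannot all hold, so neither the presence nor the direction of unequal drop-out can be taken from the article.

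**LOCF bias, assumed inputs.** The article gives no drop-out rate and no trajectory. Assume that all arms share one trajectory (no true difference), with mean improvement of 0.25 SD at week 2 and 1.00 SD from post-treatment on, and that drop-outs leave after week 2. Then

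bias at post-treatment = (difference in drop-out rates) × (improvement after the carried visit),

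against the arm with more drop-out. The second factor is 1.00 − 0.25 = 0.75 SD if week 2 is carried, and 1.00 SD if baseline is carried.

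| Drop-out, two arms | Week 2 carried | Baseline carried |
|---|---|---|
| 20% v 20% | 0 | 0 |
| 30% v 20% | 0.10 × 0.75 = 0.075 SD | 0.10 SD |
| 30% v 10% | 0.20 × 0.75 = 0.15 SD | 0.20 SD |
| 40% v 10% | 0.30 × 0.75 = 0.225 SD | 0.30 SD |

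**Effect on the group-by-time test.** This was simulated with 4,000 runs per scenario under the same assumptions: ρ = 0.5 between all visits, 30 completers per arm with drop-outs added, and week 2 carried. The type I error at nominal 0.05 (drop-out INT/IPT/CGP) was 0.033 at 20/20/20%, 0.071 at 30/20/10%, 0.157 at 40/25/10% and 0.324 at 50/30/10%. With complete follow-up it was 0.049 to 0.054.

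**Baseline.** With baseline as one of five time levels, a constant post-baseline effect appears in the treatment main effect at 4/5 of its size; the group-by-time term still uses baseline fully. For a single follow-up visit, the variance of a change score relative to baseline adjustment is 2(1 − ρ) / (1 − ρ²) = 2 / (1 + ρ): 1.54, 1.33 and 1.18 at ρ = 0.3, 0.5 and 0.7. This compares two single-visit analyses, so it only indicates what adjustment might gain over the planned multi-visit model.

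**The case against.** The strongest reply is that LOCF is labelled additional. A reader might infer that it fills the gaps in the main ANOVA, but the article does not say so, and software and estimation details may sit in a document that is not shown. That stands as far as it goes. It does not rescue the plan: without LOCF or another imputation, the named ANOVA excludes participants with incomplete rows, and the follow-up rule is a matter of conduct that an analysis plan cannot repair.

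A reader might also infer from Table 5 that INT will be penalised. The documents do not support that. The row pools drop-out with switching, switchers continue to be assessed, and the text expects similar or only slightly different retention. With equal rates, equal timing and a common trajectory, the LOCF bias is zero.

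A third inference is that LOCF would overwrite switchers' observed outcomes, because they count as drop-outs and the LOCF sentence covers all drop-outs. That is one literal reading. The same section promises their assessments on schedule, separates them from other drop-outs and gives them a post-hoc analysis. The wording is ambiguous; it is not a stated plan to discard data.

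Finally, the planned ANOVA might be said to waste the baseline measurement. It does not: baseline is a level of time and informs the group-by-time comparison.

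**Conclusion.** The point holds in this form: the article implies that drop-outs other than switchers are no longer assessed, names LOCF as its only missing-data method, and specifies a main analysis that cannot include incomplete participants without imputation. The completer result is open to selection bias, and the LOCF result is biased whenever drop-out rate or timing differs by arm.

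The size is conditional. Under the assumed trajectory with week 2 carried, it runs from 0 to 0.225 SD for gaps of 0 to 30 percentage points, and up to 0.30 SD if baseline is carried. None of the drop-out rates, the trajectory or the correlation comes from the article, and the direction cannot be fixed while its retention statements conflict. Using baseline as a covariate would be a gain in efficiency, not the correction of an error. The planned before-and-after effect size is not part of the problem, because between-arm tests are already planned.

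**What to change.** 1. Distinguish stopping therapy from withdrawing consent. Keep the already scheduled post-treatment, 6-month and 12-month assessments for therapy drop-outs who still consent. The cost is some effort to reach them; the change must be made before the data are lost.
2. Make the main analysis a likelihood-based mixed model for repeated measures in all randomised participants, by randomised arm, with arm, visit, arm-by-visit and baseline score as covariate. Use switchers' observed outcomes; each person then counts once, in the arm of randomisation, which meets the Discussion's worry about duplication. The estimate then includes the effect of permitted switching, and the post-hoc analysis of switchers can stay. Report adjusted between-arm differences with 95% confidence intervals. The cost is revised wording and a little programming.
3. The mixed model assumes that missingness depends only on observed data. Replace LOCF with a sensitivity analysis that allows missingness not at random, or keep LOCF only as a secondary sensitivity analysis that never overwrites an observed value.
4. Reconcile the retention statements in Expected Outcomes and Table 5, and separate drop-out from switching in the table. This costs only editing.

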### Data Sharing and Publication

After completion of the study, a report for publication in a peer-reviewed journal will be prepared. The manuscript will be edited/compiled according to the CONSORT statement recommendation (52–54). The study protocol has been registered at: www.clinicaltrials.gov (ID: NCT0331664; 17.10.2017). The study protocol was written according to the SPIRIT 2013, statement for reporting of trial protocols (55) and the TIDieR guidelines (56).

### Expected Outcomes

We expect all treatment arms to show similar overall rates of improvement; with differences in specific domains. Regarding symptom load, we do not expect any treatment arm to perform significantly better than the others. Regarding psychosocial functioning, we expect INT and IPT to be superior to CGP. Regarding cognitive abilities, we expect that patients participating in INT will perform better than both CGP and IPT participants.

Regarding the feasibility and implementation of the treatment arms, we expect similar retention rates in all treatment arms. Moreover, we anticipate that chronic and lower functioning participants will switch to CGP; whereas higher functioning participants may switch to INT, with lower fluctuation in IPT. Consequently, we anticipate slightly higher retention rates for IPT, followed by INT and CGP. For an overview of the expected outcomes (see Table 5).

**Table 5 T5:** Expected outcomes.

	**Intervention**		
**Expected outcomes**	**INT**	**IPT**	**Cogpack**
Overall improvement (CGI)	+	+	+
Overall functionality (GAF)	+++	++	+
Prescribed medication	+	++	+++
Drop out-switch of treatment group	+++	++	+
Completion of therapy	++	++	+++
Symptom load (PANSS)	+	+	+
Symptom perception (BSI)	++	++	+
Psychosocial functioning (mini ICF)	++	++	+
Psychosocial functioning (HoNOS)	++	++	+
Neurocognitive performance (MCCB)	+++	+	++
Speed of processing	++	+	+++
Verbal learning	+++	++	+
Working memory (non- verbal)	++	+	++
Working memory (verbal)	++	++	+
Reasoning and problem solving	+++	++	++
Visual learning	++	+	+++
Social cognition	++	++	+
Attention/Vigilance	+++	++	+++

## Discussion

Schizophrenia is a severe chronic disorder; those affected are frequently not able to cope with everyday challenges. Despite advances in treatment and an increase in treatment options the proportion of patients with schizophrenia who fully recover remains practically unchanged, this holds especially true for those requiring hospitalization for treatment (4, 57), however, for methodological reasons, those severely affected by a psychiatric disorder (i.e., those requiring hospitalization) are frequently excluded from studies testing new treatment interventions (58, 59).

The implementation of a new treatment intervention in clinical practice and moreover in an inpatient setting is a major challenge presenting a number of methodological and logistic problems. Firstly, patients hospitalized for treatment are generally more heterogeneous, with several co-morbid conditions, as well as being more severely affected than those typically included in studies. Especially patients with psychotic disorders who are more severely affected tend to have less insight and treatment motivation; consequently, they are less likely to enroll in therapy. Furthermore, the very negative and cognitive symptoms which require treatment may themselves interfere with treatment. Participants may, therefore, be unable to cope with the demands of therapy, leading to demotivation and frustration, which may lead to drop-out from therapy. We have therefore chosen to compare three treatment interventions with similar therapeutic targets and approaches, but differing participation (for patients) and implementation (for therapists) thresholds.

In clinical practice, factors relating to a patient which may affect the therapeutic outcome are considered before initiating treatment. This procedure is, however, incompatible with a randomized assignment of treatment. Furthermore, it makes it impossible to determine if a treatment is really feasible for a group of participants. Therefore, we chose to allow a switch of treatment groups after four sessions, a challenging methodological alternative which should, however, facilitate participants finding the appropriate therapy whilst allowing us to achieve our study goals. The decision to switch from one intervention to another is entirely the participant's choice. This approach strengthens the commitment of participants toward the therapy (60), by reducing feelings of failure or inadequacy which may be raised by psychometric and neurocognitive testing (61). Furthermore, we consider this approach will reduce a potential delayed selection bias.

Taking into account that participants switching treatment arms will continue their treatment, we have decided to continue the assessment of outcomes. Baseline severity will, in such cases, correspond to the time when the main therapy began. This has as a consequence that in addition to the three original treatment arms other treatment arms emerge, namely those of switching from one treatment to another. Since we are not able to accurately foresee how many participants will use this option, and if so to which treatment option they will switch, we have decided to include this in a *post-hoc* analysis. To avoid bias and duplication, we will consider participants switching groups as drop-outs in the primary analysis.

The assessment of outcomes uses a variety of instruments measuring symptom load, neuro-cognitive performance and psychosocial functionality since we expect each treatment arm to show a unique response profile (11). For symptom load, we have chosen to use the PANSS, since it is considered the most specific and validated scale for measuring change in patients with a schizophrenic psychosis (62, 63). The MCCB is regarded as the standard test battery for use with patients diagnosed with schizophrenia; it is claimed as both robust to learning effects and sensitive to change (47). Taking into account that improvements in symptomatology and neuro-cognition should lead to increased autonomy, we have chosen the mini-ICF-APP to assess psychosocial-functioning independently of the main diagnosis (40, 64, 65). Using this set of outcome measures, we expect to assess all facets of the interventions, whilst facilitating the interpretation and comparison of our results with those from previous studies (63).

We anticipate an overall improvement in all participants, regardless of group allocation. This may be attributable to pharmacological treatments administered to the participants. For the same reason, we do not anticipate significant differences in symptom load. However, we do not exclude to find differences in dose equivalents of administered medication, primarily antipsychotics and benzodiazepines. Furthermore, we hope for a reduction of polypharmacy. In order to quantify this effect; medication, respectively dose and dose equivalents, will be taken into account as possible confounders (66). Pharmacological treatment will not be restricted since we consider withholding or delaying pharmacological treatment for methodological or design purposes to be unacceptable; furthermore, in clinical practice, psychological interventions are used as an add-on to pharmacological therapy (11). Offering just a single psychotherapeutic treatment could be ineffective for some patients and at worst detrimental, which could lead to treatment abandonment (67). An intervention which is neither accepted nor tolerated by participants should not be imposed on them.

The allocation of a patient to a treatment arm which does not meet his needs is considered to be unacceptable and may have detrimental effects. To avoid this situation, we have decided to allow participants to switch groups under particular conditions. We consider this approach to be both appropriate and compatible with the trial objectives since we are also interested in evaluating feasibility. In order to minimize the effect of group changes on the primary and secondary outcomes of the study, and to have similar treatment duration and number of sessions, we have chosen to conduct a second assessment prior to a (potential) change of groups. We consider 2 weeks, respectively four sessions, sufficient to determine the suitability and safety of a therapy. INT in outpatient setting shows low drop-out rates and high rates of attendance which indicates a high level of acceptance and motivation and lends support feasibility (29). Another aim of this study is to evaluate whether this also applies to inpatient settings.

Another challenge of this trial was the adaptation of a treatment (INT) designed for outpatients to an inpatient setting (29, 38). The hierarchical structure of the intervention, the density of the therapeutic sessions, and the duration of the therapy had to be taken into account together with the fact that the original therapeutic design foresees closed therapeutic groups (27). For its implementation in an inpatient setting, we subdivided the intervention into modules or blocks comprising of four sessions, allowing the participants to join the therapy at specified times thus allowing for (semi)closed groups. The disadvantage of this approach lies in the hierarchical structure of both INT and IPT interventions (23, 27), which leads participants potentially starting with a more challenging topic; to minimize this effect blocks or modules also had a bottom-up structure allowing new participants to integrate quickly into the group.

Lower functioning patients with low functioning, including those with chronic schizophrenia, seem to benefit from higher frequency psychotherapy (21, 68). We, therefore, concluded that two weekly sessions of 90 min would fulfill this demand. Taking into account the usual length of stay in our unit (6 to 8 weeks), together with current guidelines (17–19) we have chosen to offer at least 16 sessions to participants. For methodological reasons it was not possible to condense both therapeutic interventions to this number of sessions, therefore IPT, INT and CGP have been adapted to 20 sessions programs, respecting the specifications of the treatment manuals.

We considered this to be compatible with the average length of stay in our unit, since some patients remain in treatment for more than 8 weeks. Participants are also encouraged to continue participation after discharge. Although we consider that the completion of a treatment programme to be an important factor determining response, evidence suggests that response is not associated with treatment duration and number of sessions (10).

There is reason to believe that the three treatment arms will differ from one another due to top-down and integration effects on multiple domains. In respect of social- and neuro-cognition, we expect INT and IPT to outperform CGP (36, 69). Nevertheless, we cannot rule out that CGP may also lead to improvements in neuro-cognitive abilities, in particular MCCB domains tested on the computer due to learning and practice effects (12, 70). We expect INT participants to achieve a higher psychosocial performance than CGP, but similar to those of IPT. Although INT and IPT have common roots, applying similar technics for social cognition (23, 27, 37), we expect INT to deliver better outcomes due to its higher complexity and integrative approach (see Table 5).

In our study, we wish to evaluate the feasibility of a psychotherapeutic intervention in a unit specialized for the treatment of chronic and low functioning patients with a schizophrenic psychosis. Therefore, the effort required to implement such regular group psychotherapy will also be taken into account. The IPT treatment programme is manualized and has traditionally been delivered by nursing staff after an introductory seminar and workshop (23). The implementation of INT is more challenging since it also requires a trained psychotherapist (27). CGP, on the other hand, is easily implemented and requires practically no training to deliver (26, 71, 72). However, professional experience is a significant factor predicting therapy outcome. Moreover, the therapist variable is an essential factor relating to motivation to participate in the therapy and influencing drop-out rates (73–75). Consequently, all therapists running groups in this study will receive regular supervision and training.
